### Allocation and sequence generation

Randomisation will be done at the PHC level, separately for Tumkur and Wardha districts. Allocation sequence will be independently generated by the study biostatistician. Eight PHCs will be included in the cRCT, with 1:1 allocation ratio.

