### Sample size

The sample size was calculated by considering a 5% detection rate of depression at primary care level [9, 10] and assuming a difference in detection rate by 20% between the intervention and control arm. Assuming an equal cluster size of 300, we will require 4 PHCs in each arm. Considering 20% attrition rate, intra-class correlation (ICC) as 0.1 [43], with 80% power, 5% alpha error for two-sided test, the minimum sample size required is 1200 adults per arm. Assuming the usual recovery rate for depression at the primary level to be 54% and an expected difference of 20% in the recovery rates between intervention and control arms, with 80% power, 5% alpha error for two-sided test, the required estimated sample size is 89 patients in each arm. Therefore, a minimum of 1200 participants per arm will be sufficient.

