### Statistical methods

The qualitative data will be audio-recorded and transcribed verbatim. The transcriptions and the field notes from IDIs and FGDs will be manually coded. An inductive-deductive approach will be used to identify key themes and sub-themes. Reporting will be done using the Consolidated Criteria for Reporting Qualitative Studies (COREQ) checklist [49]. 

After checking for normality, continuous data will be expressed using mean (standard deviation) or median (interquartile range). Categorical data will be described using frequency and percentages. The difference in the detection and recovery rates between intervention and control arms, as well as associated risk factors for depression, will be compared using generalised estimating equation (GEE) analysis with a log link and exchangeable correlation structure to adjust for cluster effects. The change in EQ-5D-5 L scores during the follow-up will be compared between two groups using a mixed linear model. A p-value less than 0.05 will be considered significant. Missing data will be handled using multiple imputation methods.

Standard health economic methods will be applied to determine the incremental cost-effectiveness ratio (ICER) based on the costs and outcomes associated with the intervention. Sensitivity analyses will be conducted to test the robustness of the results. All analyses will be carried out using R software. Tree age software will be used to perform cost-effectiveness analyses.

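### With four PHCs per arm and no small-sample method named, a default GEE analysis would not hold the stated 5% error rate: about 14% in most settings and about 23% at the protocol's own inputs

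*Protocol article*

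**What the plan says.** All references are to the protocol article.

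- **Statistical methods:** detection and recovery rates are compared between arms "using generalised estimating equation (GEE) analysis with a log link and exchangeable correlation structure to adjust for cluster effects". The decision rule is "A p-value less than 0.05 will be considered significant". The software is R.
- **Allocation and sequence generation:** "Eight PHCs will be included in the cRCT, with 1:1 allocation ratio", and "Randomisation will be done at the PHC level, separately for Tumkur and Wardha districts". With four PHCs drawn from each site (Study setting), that is two per arm in each district.
- **Sample size:** the planning inputs are "considering a 5% detection rate of depression at primary care level", "assuming a difference in detection rate by 20% between the intervention and control arm" and "Considering 20% attrition rate, intra-class correlation (ICC) as 0.1", with 80% power and a two-sided 5% test. The result is "Assuming an equal cluster size of 300, we will require 4 PHCs in each arm", or 1200 adults per arm. Recovery is planned separately at 54% with a 20-point difference and 89 patients per arm.

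The article does not say which GEE standard error will be used, which distribution the test statistic will be referred to, or whether any correction for few clusters applies.

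**The concern.** The robust (sandwich) variance that usually accompanies GEE is justified when the number of clusters is large. With four clusters per arm it is too small on average, and the usual Wald test adds to the error by using a normal rather than a t reference. Both faults act in the same direction: p-values too small, intervals too narrow. The sample size section promises a two-sided 5% test. If the default output is used, the trial could declare the intervention effective by chance several times as often as that, and the article hopes the findings will influence policy.

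**Working it through.** **1. The plan's own figure.** The target is 4 × 300 = 1200 per arm at two-sided 5%. Reading the difference as 5% against 25%, the pooled two-proportion formula gives 49 per arm before clustering. The design effect is 1 + (300 − 1) × 0.1 = 30.9, so 49 × 30.9 = 1514, and 1514 / 0.8 = 1893 after 20% attrition. With 240 analysed per PHC the design effect is 24.9, giving 1220 before and 1525 after attrition. The 1200 is therefore not reproduced once attrition is included. That is a separate matter, and nothing below depends on it. The formula itself makes no allowance for having only eight clusters.

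**2. Large-cluster limit.** With k equal clusters per arm and arm as the only covariate, the robust variance of the log ratio is the sum over arms of Σ(p_i − p̄)² / (k² p̄²). It divides by k² where an unbiased version divides by k(k − 1), so with k = 4 it is 3/4 of what it should be. Referred to ±1.96, the false-positive rate is 2 × P(t₆ > 1.96 × √0.75) = 2 × P(t₆ > 1.697) = 0.141, whatever the ICC.

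**3. Simulation under no effect.** Beta-binomial, 4 + 4 PHCs of 300, 200,000 runs per setting, uncorrected robust errors, normal reference:

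| Detection in both arms | ICC 0.01 | ICC 0.02 | ICC 0.05 | ICC 0.1 |
|---|---|---|---|---|
| 5% | 14.7% | 15.4% | 18.1% | **23.0%** |
| 10% | 14.2% | 14.5% | 15.6% | 17.7% |
| 15% | 14.1% | 14.2% | 14.8% | 16.0% |
| 25% | 14.0% | 13.9% | 14.2% | 14.3% |

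Thirteen of the 16 cells lie between 13.9% and 16.0%. The bold cell uses the article's own inputs; with 240 per PHC it is 22.8%. The rise above 14% comes from skewness. At 5% and ICC 0.1 the first beta parameter is 0.05 × 0.9 / 0.1 = 0.45, so most PHC rates lie near zero and a few are high. Runs with no detections in one arm (at most 0.4%) were left out.

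**4. Direct GEE fits** (log link, Poisson working variance, exchangeable, 1000 fits per setting):

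| Setting | Robust, z | Model-based, z |
|---|---|---|
| 5%, ICC 0.1 | 23.5% | 10.1% |
| 5%, ICC 0.05 | 17.8% | 11.0% |
| 5%, ICC 0.02 | 16.5% | 14.0% |
| 25%, ICC 0.1 | 13.3% | 9.4% |

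Adding a district term with robust errors and z made it worse: 18.0% to 26.6% in three settings of 500 fits each.

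**5. Recovery.** The article does not give the number of recovery patients per PHC. Its 89 per arm is 89 / 4 ≈ 22, and 5% of 300 is 15, so I assume 10 to 22. At 54% recovery the uncorrected robust z-test then rejects in about 12.5% to 14%.

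**6. Candidate repairs at 5% detection and ICC 0.1.**

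- Kauermann-Carroll variance with t on 6 df: about 10%.
- Mancl-DeRouen variance with t on 6 df: 6.6%.
- Regression of eight PHC proportions on arm and district, t on 8 − 3 = 5 df: about 3%, and 3.0% to 5.1% over detection of 5% to 25% and ICC of 0.01 to 0.1.
- Permutation test stratified by district: C(4,2)² = 36 allocations, so the smallest two-sided p is 2/36 = 0.056. It can never meet the 0.05 rule.

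**7. Power of the valid test, 5% against 25%.** At ICC 0.1 the variance of a PHC proportion is p(1 − p)(0.1 + 0.9/300). This is 0.0475 × 0.103 = 0.00489 in control and 0.1875 × 0.103 = 0.01931 in intervention. The standard error of the difference is √((0.00489 + 0.01931)/4) = 0.0778, and 0.20 / 0.0778 = 2.57. That is also the 5-df critical value, so power is only a little over one half. Simulation gives about 57% at ICC 0.1 and about 83% at ICC 0.05.

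**The case against.** The strongest reply is that the failing ingredients are not in the text. The article names neither the sandwich variance nor the normal reference, and a condensed article may leave both to an analysis plan that is not shown. A log-link GEE on eight clusters can also be run close to level: the Kauermann-Carroll variance with t on 6 df gave 5.0% to 6.1% in 13 of the 16 settings above.

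Much of this stands. A reader might infer that the protocol commits the trial to a test with a 14% to 23% error rate. It does not; the figures are conditional on the default analysis. Nor does 23% apply throughout: it needs 5% detection in both arms, ICC 0.1 and skewed PHC rates. Recovery should not be given the same range either, since the rate there is lower and rests on an assumed number per PHC.

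What the reply does not remove is this. The article does fix the model, the threshold and eight clusters, and claims a 5% test. Neither standard GEE error referred to the normal delivers that. The usual corrections differ materially at the article's own inputs, so the choice cannot be treated as routine detail. The stated 80% power is also not available from the cluster-level test that does hold its level at those inputs.

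**Conclusion.** The point holds in conditional form. If the GEE is run with uncorrected robust errors and a normal reference, the false-positive rate for the primary comparison is roughly 2.8 times the nominal 5% in the large-cluster limit (14.1 / 5) and 4.6 times at the article's planning inputs (23.0 / 5). Model-based errors reduce the excess but do not remove it. Recovery is affected to a somewhat smaller degree.

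The 14% floor follows from four clusters per arm alone. The excess above it depends on the beta-binomial model, a low detection rate and the article's ICC of 0.1. The power figures assume that the 20% difference means 5% against 25% in absolute terms. Because this concerns the primary test, it should be settled before any comparison by arm is seen; a change made afterwards would look driven by the data.

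**What to change.** In Statistical methods, or in the analysis plan with a matching sentence in the protocol:

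1. **Primary test:** linear regression of the eight PHC detection proportions on arm and district, with a t reference on 5 df, reporting the risk difference and its t-based 95% interval.
2. **GEE:** keep the log-link model for the ratio estimate only, with a named small-sample variance and a t reference. Mancl-DeRouen is closer to level than Kauermann-Carroll at 5% detection and ICC 0.1. Require a small-sample method for recovery as well.
3. **Permutation:** do not rely on a district-stratified permutation test for significance at 0.05.
4. **Sample size:** restate power for the test actually used, over a range of ICC.

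The wording is a paragraph, but the cost is more than that. On a like-for-like scale, intervals widen by about half: 2.571 / (1.96 × √0.75) = 1.51. Power at the article's inputs is about 57%, not 80%; it reaches about 83% only if the ICC is nearer 0.05. Enrolling more adults per PHC would barely help, because at ICC 0.1 the term 0.1 + 0.9/m is already 0.103 at m = 300 and cannot fall below 0.1. The team must either add PHCs or state the lower power openly.

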**Fig. 2 Fig2:**
[figure not shown]
Consort flow diagram

Phase I: In this, baseline data collection using outpatient records in all study PHCs will be carried out to determine the PHC footfall, number of adults diagnosed, managed, or referred for mental health conditions over the past six months.

Phase II: PHCs will be randomised and allocated into the intervention arm (*n* = 4) and the control arm (*n* = 4). Subsequently, intervention package will be delivered to HWs in the intervention PHCs. HWs at the control PHCs will receive a one-day sensitisation session on mental health conditions, including brief psychoeducational counselling on depression.

Phase III: Screening, assessment, psychological counselling of adult participants by HWs, and referrals will take place during this phase. In both intervention and control PHCs, adults attending the study PHCs will be enrolled consecutively ss per the eligibility criteria. They will be allotted to each HW depending on the availability of HW in the PHCs for screening, assessment, and management of depression.

Phase IV: In both arms, participants identified with mild depression will receive psychological counselling from HWs and will be followed up as outlined in the pilot phase. Each follow-up counselling session will last 10 min per participant. PRS will give telephonic reminders to participants to reduce dropouts. Screening, assessment, and management of mild depression will be done using application in intervention PHCs and through usual care in control PHCs by the HW.

Validation by PRS: At the time of baseline assessment, the PRS will validate all participants identified with mild depression by HWs. Along with this, PRS will also randomly conduct a validation check PHQ 9 scores in participants identified as normal by HWs. To document changes in PHQ-9 scores, the PRS will administer the PHQ-9 to participants at all follow-up visits. PRS will do a health-related quality of life (HRQoL) assessment at baseline and the last follow-up.

Referral: Participants with PHQ-9 scores ≥ 10 or having suicidal ideation will be referred to the DMHP psychiatrist at the sub-district hospital. The PRS will contact participants telephonically to ensure they receive appropriate care. Throughout the study, the research team will provide weekly supportive supervision to all HWs in both arms to provide feedback and address any issues they may face.

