### Data collection methods

Qualitative interviews will be conducted using IDI and FGD guides, prepared by the research team. Pre-training and post-training knowledge of HWs will be assessed using mhGAP knowledge questionnaire [44]. 

Screening and assessment of participants will be done using the PHQ-2 and PHQ-9. PHQ-2 has been recommended as a pre-screen prior to administering PHQ-9 items [45]. A score of ≥ 3 requires further assessment with PHQ-9 to determine severity of depression. The PHQ-9, designed for primary care settings, consists of 9 items which measure the frequency of depressive symptoms over the past fortnight. A multicentric Indian study reported PHQ-9 reliable for screening depression by HWs [46]. Table 5 provides the operational definitions of our study.Acceptability and feasibility of the intervention will be assessed using AIM instrument [47]. 

The HRQoL will be measured at baseline and endline by the PRS using EUROQUAL instrument (EQ-5D-5 L), the norms of which are available for the Indian population [48]. 

Detailed costing of every single ingredient will be gathered for doing cost-effectiveness analysis.

**Table 5 Tab5:** Operational definition for PHQ-9 used in the study

Operational definition	PHQ-9 score
*1. Normal*	< 5
*2. Mild depression*	5–9
*3. Moderate depression*	≥ 10
*4. Severe depression*	≥ 15
*5. Recovery*	< 5

The socio-demographic details from participants will be used to generate a unique identification number (UID).

In the intervention arm, screening, assessment, and counselling of participants by HWs, validation by the PRS and follow-up data will be captured in the mobile application. This data will get stored in the application backend which can be downloaded in Microsoft Excel format. In the control arm, screening, assessment, follow-up, and validation data will be captured using a case record form (CRF). This along with the HWs knowledge scores, EQ-5D-5 L scores, AIM scores, and costing data will be collected using Epicollect5 with appropriate quality checks to minimise errors. Respective site PIs will constantly monitor all the data captured through the application and by Epicollect5.

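### EQ-5D-5L is compared as a change between arms with no stated adjustment for its baseline value, which gives up precision unless a baseline term is fitted

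*Protocol article*

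**What the plan says.** The whole EQ-5D-5L analysis is one sentence in Statistical methods: "The change in EQ-5D-5 L scores during the follow-up will be compared between two groups using a mixed linear model". It names no fixed effects, random effects or coding of the response.

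The measurement times are clear. Under Implementation (validation paragraph): "PRS will do a health-related quality of life (HRQoL) assessment at baseline and the last follow-up". Under Data collection methods: "The HRQoL will be measured at baseline and endline by the PRS using EUROQUAL instrument". So there is one baseline and one endline value per participant.

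The people with an endline value are those who are followed up. Under Implementation, the paragraph on the fourth phase says: "In both arms, participants identified with mild depression will receive psychological counselling from HWs and will be followed up as outlined in the pilot phase". How they are found differs by arm: "Screening, assessment, and management of mild depression will be done using application in intervention PHCs and through usual care in control PHCs by the HW".

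Table 3 lists HRQoL scores fourth under Objective 2. The abstract names detection of depression as the primary outcome. The article states no power, SD, target difference, ICC or baseline-endline correlation for EQ-5D-5L.

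**The concern.** With one baseline and one endline value, the sentence has two natural readings: a model of each person's change, or a repeated-measures model with an arm-by-time term and free baseline means. In complete data both give the same arm contrast, and both fix the coefficient on the baseline value at 1. When the two SDs are similar, the best-fitting coefficient is rho, which is below 1. Fixing it at 1 adds noise.

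Precision may be scarce. There are eight PHCs, four per arm. The Sample size section assumes 5% detection in control and a 20% difference, read here as 25% in the intervention arm. If those rates apply to the followed group, 300 adults per PHC give 15 and 75 cases. After 20% attrition, 12 and 60 per PHC remain.

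The second issue is what happens when the two followed groups start at different EQ-5D-5L levels. Part of such a gap may be chance or a passing state, which shrinks by endline whatever the treatment does. A change score counts that shrinkage as an effect.

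**Working it through.** The article states no EQ-5D-5L figure that could be reproduced, so the check concerns the method.

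**Inputs.** Two measurements per person (Implementation; Data collection methods). Assumed: equal SD at both times, scaled to 1, and rho from 0.2 to 0.8. Clustering is left out of the formulas; the ratios carry over if rho is the same at PHC and person level.

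**Precision.** The change-score variance is proportional to 2(1-rho). The baseline-adjusted variance is proportional to 1-rho² = (1-rho)(1+rho). Their ratio, adjusted to change, is (1+rho)/2.

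| rho | change, 2(1-rho) | adjusted, 1-rho² | adjusted / change | SE, change / adjusted |
|---|---|---|---|---|
| 0.2 | 1.60 | 0.96 | 0.60 | √(1/0.60) = 1.29 |
| 0.5 | 1.00 | 0.75 | 0.75 | √(1/0.75) = 1.15 |
| 0.8 | 0.40 | 0.36 | 0.90 | √(1/0.90) = 1.05 |

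**Baseline difference.** Let D be the baseline gap between the followed groups (intervention minus control), let the treatment do nothing, and let a fraction k of D remain at endline.

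- Change-score bias: kD - D = (k-1)D.
- Baseline-adjusted bias: kD - rho·D = (k-rho)D.

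Three cases follow.

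- *Chance or transient gap, k = rho.* The change score is off by -(1-rho)D and the adjusted estimate by 0. For an illustrative D of 0.05, the change score is off by -0.040, -0.025 and -0.010 at rho 0.2, 0.5 and 0.8.
- *Fully lasting gap, k = 1.* The change score is off by 0 and the adjusted estimate by (1-rho)D. At D = 0.3 SD and rho = 0.5 that is 0.5 × 0.3 = 0.15 SD.
- *In between.* Adjustment is the less biased of the two when k is below (1+rho)/2, that is below 0.60, 0.75 and 0.90 at rho 0.2, 0.5 and 0.8.

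**Simulation check** (2,000 runs, 100 per arm, rho 0.5, no treatment effect, clustering ignored):

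| Baseline gap | Change score, mean (SD) | Adjusted, mean (SD) |
|---|---|---|
| Chance only | -0.002 (0.141) | -0.002 (0.123) |
| Lasting, 0.3 SD | -0.001 (0.144) | +0.147 (0.127) |

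With chance gaps only, both methods average zero over repeated trials. Within a given trial, the change-score estimate moves by -0.5 per unit of baseline gap and the adjusted estimate by 0.0. With a lasting gap, the roles reverse, as the formulas say.

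**The case against.** The strongest reply is that this is a one-sentence summary in a condensed article. The sentence does not exclude a baseline covariate, and covariate lists are often left to a statistical analysis plan, which is not shown. A model of change with baseline as a covariate would fit the sentence and would give the same arm coefficient as the endline model proposed below. This stands as a limit on wording: a reader might infer that the trial will definitely use unadjusted change scores, and the article does not establish that. What remains is that the article makes change the compared quantity and names no baseline term, although it gives the link and correlation structure for the detection and recovery analysis in the same section. On either natural reading the baseline coefficient is fixed at 1.

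The second reply concerns bias. A reader might infer that any baseline difference between the followed groups becomes a false effect under change scores. The documents do not support that. The groups are formed after randomisation by detection that differs between arms, so a gap may be real and lasting. Then the change score is unbiased and adjustment introduces the error. The documents do not say which kind of gap to expect. Nor do they show that a gap is likely: mild depression is a single PHQ-9 band, 5 to 9 (Table 5), and the research scientist validates every case that HWs identify as mild. This reply stands in full.

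Third, no gain in power can be read from the article, because it claims no power for EQ-5D-5L. That also stands, so the size is given only as a ratio of standard errors.

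**Conclusion.** The point holds as one of precision. Unless a baseline term is fitted, the EQ-5D-5L comparison has a standard error about 29%, 15% or 5% larger than the same data allow at rho 0.2, 0.5 or 0.8. This rests on equal SDs at the two times and an assumed rho. A chance or transient baseline difference D also carries into the estimate as -(1-rho)D.

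The bias argument goes no further. For a lasting difference produced by arm-dependent detection, the adjusted estimate is the biased one, by (1-rho)D. Neither analysis removes the selection that arises because the followed groups form after randomisation.

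The consequence is modest, since this is a secondary outcome. The improvement is worth making because it uses data the trial already plans to collect.

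**What to change.** In Statistical methods, replace the EQ-5D-5L sentence with wording to this effect: *Endline EQ-5D-5L will be compared between arms using a linear mixed model with arm, baseline EQ-5D-5L and district as fixed effects and PHC as a random effect; the unadjusted comparison of change scores will be reported as a sensitivity analysis.* District belongs in the model because randomisation is done separately in the two districts.

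The cost is a sentence of analysis text, with no new data, visits or staff. Baseline EQ-5D-5L varies between individuals and takes no PHC-level degrees of freedom. District takes one (8 PHCs less 2 arm means leaves 6; less district leaves 5).

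The downside should be stated alongside: the two analyses can disagree if a baseline difference between the followed groups persists, and neither corrects for who was detected in each arm. If they disagree, report both with the baseline EQ-5D-5L of each followed group, and do not treat the adjusted result as settling the matter.
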